**Methods:**

The study employs a three-arm, double-blind, randomized, superiority-controlled design. Participants are randomly allocated in a 1:1:1 ratio to one of three groups receiving: (1) real PL and real tES, (2) real PL and sham tES, and (3) placebo PL and sham tES. Each participant undergoes 10 sessions per block (~ 1 h each), with a total of three blocks. Assessments are conducted at six time points: baseline, interim 1, interim 2, post-intervention, 1-month post-intervention, and 2-month post-intervention. The primary outcome is the mean deviation of the 24-2 visual field measured by the Humphrey visual field analyzer. Secondary outcomes include detection rate in the suprathreshold visual field, balance and gait functions, and electrophysiological and biological responses. This study also investigates changes in neurotransmitter metabolism, biomarkers, self-perceived quality of life, and psychological status before and after the intervention.

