### Objectives {7}

#### Specific objectives

The aims of this study are to (1) compare the effects of monotherapy (either PL or tES) and combined therapy (PL + tES) on improving visual field function; (2) examine whether the interventions influence brain neural activity, and concentrations of neurotransmitters in the brain and blood; (3) investigate the degree to which enhancements in visual field or brain neural activity, brought about by the interventions, act as moderating factors in the improvement of mobility performance, mental health, fear of falling, and QoL; and (4) optimize the training protocol and the optimal dosage for achieving maximal intervention effect in glaucoma patients.

Hypotheses:The combination of PL and tES will result in greater visual field improvements than monotherapy.The intervention effect will increase with longer training duration.The improvement in the visual field induced by the interventions will be accompanied by changes in brain activities and blood biomarkers.An improved visual field will contribute to better balance function, gait performance, and QoL. It will also decrease fear of falling and symptoms of depression or anxiety in glaucoma patients.

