### Trial design {8}

This protocol is designed for a three-arm, double-blind, randomized, superiority-controlled design with 1:1:1 allocation. Figure 1 shows the flow chart of this study.

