## Interventions

### Explanation for the choice of comparators {6b}

Although both PL and tES have shown beneficial effects in restoring visual functions in patients with glaucoma, it is still unclear whether a combined approach can offer greater benefits than monotherapy. Therefore, our goal is to compare the effectiveness of combined PL and tES with monotherapy in improving the visual field in glaucoma patients. Through this comparative study, we aim to understand the potential combined effects and identify the optimal approach for enhancing visual rehabilitation in glaucoma patients.

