#### Primary outcome

Visual field test is measured monocularly using the 24–2 and 10–2 Swedish interactive threshold algorithm (SITA) standard tests by Humphrey visual field analyzer (HFA, Carl Zeiss Meditec Inc., California). The mean deviation (MD), pattern standard deviation (PSD), and visual field index (VFI) are recorded and the MD of 24–2 visual field test is used as primary outcome of intervention effectiveness. HFA visual field test is conducted at six time points, from T1 to T6.

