## Statistical methods

### Statistical methods for primary and secondary outcomes {20a}

At the conclusion of this project, we will perform statistical analysis based on the intention-to-treat (ITT) principle. For the primary outcome, the differences of MD measured using the 24–2 SITA HFA will serve as an indicator of the effectiveness of interventions. Among the three groups, the intervention group showing the greatest improvement in MD will signify the strongest impact of rehabilitation. Additionally, changes in MD across six time points (baseline, interim 1, interim 2, post-intervention, 1-month post-intervention, and 2-month post-intervention) will reveal the dose-response relationship and recovery duration.

To address inter-individual variability, we will employ a linear mixed model with intervention type and time point as the fixed effect, and baseline MD value as the covariate. A dummy-coding scheme with the placebo PL + sham tES condition as the reference level will be utilized. Initially, a full model will be fitted, and if convergence issues or overfitting arise, adjustments will be made to the random intercept and slope. Model comparison will be conducted using a likelihood-ratio test to evaluate the adequacy of the current model relative to alternative models without the fixed effect. The level of statistical significance for analysis is set at a two-sided *p* < 0.05.

To address the potential attrition and missing data due to participant drop-out, we will conduct sensitivity analyses using multiple imputation methods. Specifically, we will employ the fully conditional specification (FCS) method. This method allows for the imputation of missing data for multiple variables with different distributions. By conducting these sensitivity analyses, we aim to assess the robustness of our primary analysis results to potential attrition bias and missing data. The multiple imputation approach will provide a principled way to handle missing data, ensuring that our conclusions are not unduly influenced by the potential non-random nature of missing data.

The analyses of secondary and exploratory outcomes will follow a similar approach to that of the primary outcome. A detailed statistical analysis plan for secondary and exploratory outcomes is being developed and will be reviewed of by the steering group prior to data analysis.

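### The primary analysis names no test of PL + tES against PL alone, the one contrast that answers Hypothesis 1, and compares the active arms only by which gained most MD

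*Protocol article*

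**What the plan says.** The question is stated twice. The Specific objectives give as first hypothesis: "The combination of PL and tES will result in greater visual field improvements than monotherapy". The section on the choice of comparators {6b} says "our goal is to compare the effectiveness of combined PL and tES with monotherapy in improving the visual field in glaucoma patients". The trial is a "three-arm, double-blind, randomized, superiority-controlled design with 1:1:1 allocation". Its arms are real PL with real tES, real PL with sham tES, and placebo PL with sham tES. No arm receives tES without real PL.

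For the outcome, "the MD of 24–2 visual field test is used as primary outcome of intervention effectiveness". The statistical methods section {20a} then fixes four things:

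- the model: "a linear mixed model with intervention type and time point as the fixed effect, and baseline MD value as the covariate";
- the coding: "A dummy-coding scheme with the placebo PL + sham tES condition as the reference level will be utilized";
- a likelihood-ratio comparison with models that omit the fixed effect, and a two-sided 0.05 significance level;
- a reading of the result: "Among the three groups, the intervention group showing the greatest improvement in MD will signify the strongest impact of rehabilitation".

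The sample size section {14} gives 80% power for a difference among the three groups.

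**The concern.** None of the tests named in {20a} is a test of the combination against PL alone. The two arm coefficients compare each active arm with placebo. The likelihood-ratio test can show that the arms differ somewhere, but not which ones. The only sentence that sets the active arms against each other says that the largest observed gain carries the meaning, with no test, interval or margin attached.

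A team following this text could report that tES adds to PL in two unsupported ways. It could note that the combined arm had the highest mean. Or it could note that the combined arm was significant against placebo while PL was not. Neither is evidence of a difference between the two real-PL arms, and that difference is the trial's headline question.

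**Working it through.** **The plan's own figure.** Take G*Power's multiple-regression F test with f² = 0.1, alpha 0.05, power 0.80 and noncentrality f²·N. Three tested predictors need N = 114, and 114/0.8 = 142.5, rounded up to 143. The next multiple of 3 is the stated 144. Two tested predictors (the two arm dummies) give 100, and 100/0.8 = 125. The article does not state the number of predictors, so this match is an inference. On either count the figure belongs to an overall test, not to the contrast between the real-PL arms.

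**Which contrast answers the hypothesis.** Write the arm means as C (real PL + real tES), P (real PL + sham tES) and S (placebo PL + sham tES). With S as reference:

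- β1 = C − S
- β2 = P − S
- β1 − β2 = C − P

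Hypothesis 1 concerns C − P. The model can estimate it, but {20a} does not name it.

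**Inputs for the error rates.** 144/3 = 48 per arm. With 20% dropout, 48 × 0.8 = 38.4, taken as 38 completers. Assumptions: one visit, outcome in SD units, no precision gain from the baseline covariate or repeated measures, and a true PL effect over placebo of d = 0.3, 0.5 or 0.63 SD. The article gives no MD difference or SD, so d is shown as a range. The standard error of a difference between two arms is √(2/38) = 0.229 SD.

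**Case: tES adds nothing (C = P = S + d).** By symmetry, the chance that C has the highest mean is half the chance that S does not. Simulation gives:

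| d (SD) | C ranked first | C significant vs S, P not | Direct C − P test favours C |
|---|---|---|---|
| 0.3 | 48.5% | 13% | 2.5% |
| 0.5 | 50% | 16% | 2.5% |
| 0.63 | 50% | 12% | 2.5% |

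If no arm has any effect, C is still ranked first 1 time in 3.

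**Power of the direct contrast.** Power is about Φ(δ/0.229 − 1.96), where δ is the true C − P difference in SD units.

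- δ = 0.5: Φ(2.18 − 1.96) = Φ(0.22), about 59%; 58% with the t distribution.
- δ = 0.4: about 41%.
- δ = 0.3: about 26% (25% with t).
- For 80% power, δ = (1.96 + 0.84) × 0.229 = 0.64 SD. With all 48 per arm, it is 2.80 × √(2/48) = 0.57 SD.

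**Effect of an omnibus gate.** Suppose C − P may be tested only after a significant three-arm test. At δ = 0.5 with P equal to S and 38 per arm, power falls from 58% to 50%.

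**The case against.** The strongest reply is that dummy coding is only a parameterisation. The missing contrast is the difference of two coefficients in the planned model, so nothing blocks it. That is right. A reader might infer that the placebo reference level makes the comparison impossible, and the documents do not support that. What is missing is the naming of the contrast.

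Second, {20a} does contain an error-controlled test: the likelihood-ratio comparison, at a stated two-sided 0.05. A reader might infer that superiority will be claimed with no test at all, or that error is inflated by unadjusted pairwise testing. The text says neither. Three ungated pairwise tests at one visit would have about 12% familywise error. If the likelihood-ratio test were used as a gate, simulation gives 5.0%. The article does not say whether it is a gate. Nor does it propose separate tests at each of the five post-baseline visits, so no error rate can be charged to such a plan. The test remains global and does not identify the arm that differs.

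Third, the ranking sentence may be meant descriptively. That is possible, but it stands in the primary-outcome methods and states what the largest gain will mean.

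Fourth, a SAP may name the contrast. The blinding section {17b} mentions a prespecified plan for primary and secondary analyses. The plan that {20a} describes as in development is for secondary and exploratory outcomes. If the unseen SAP does name the contrast, the published sentence conflicts with it and still needs changing. The statement in {20b} that no additional analyses will be done sits under subgroup and similar analyses, and does not exclude a primary contrast.

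**Conclusion.** The point holds in a limited form. The hypothesis and the comparator rationale ask for combination versus PL alone. The primary analysis names no test of that, and its one statement about the active arms is an untested ranking. This is a stated rule that can mislead, not merely an omitted detail.

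When tES adds nothing to an effective PL, the ranking favours the combination in about 48–50% of trials, and the split-significance pattern appears in about 12–16%. A direct two-sided test would wrongly favour it in 2.5%. These figures rest on 38 completers per arm, one visit, and an assumed PL effect of 0.3 to 0.63 SD. They matter to the extent that the ranking, or a comparison of the two placebo-referenced p-values, is used to answer Hypothesis 1. The coding is not at fault, and no figure for multiplicity across visits is warranted.

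**What to change.** Replace the ranking sentence in {20a} with a prespecified primary contrast: (real PL + real tES) minus (real PL + sham tES) in 24-2 MD. Estimate it as the difference of the two arm coefficients in the planned mixed model, with a 95% CI, and test it at two-sided 0.05. A single named contrast needs no omnibus gate, and a gate would cost power.

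State one primary visit. T4, the post-intervention assessment, is one candidate, but the article does not designate any visit and the choice is the investigators'. Include the arm-by-time term that a visit-specific contrast needs; {20a} does not list it, although its unspecified full model may contain it. Make the placebo comparisons and the other visits secondary or supportive.

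The change needs no new data or participants. No interim analysis is planned and unblinding follows data lock, so it can be made before anyone sees results by arm. The cost is in power: the stated 80% is for a difference among three groups. Power for the new contrast must be stated separately and may be lower, about 58% at an assumed 0.5 SD under the conditions above. Baseline adjustment and repeated measures may raise it, but the article gives no figures from which to say by how much.

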## Discussion

The progressive and irreversible nature of visual impairment caused by glaucoma has a significant profound impact on QoL and poses a serious public health concern. Consequently, there is an urgent need for novel rehabilitation methods that can enhance functional vision and improve the overall well-being of glaucoma patients.

The GREAT study aims to investigate the individual and combined effects of tES and PL on visual field, functional performances, brain activity, and various patient-reported outcomes in glaucoma patients. Importantly, this study examines the dose-response relationship and follow-up of any treatment effects, providing insights into the optimal dosage and duration of these interventions. Furthermore, the study monitors changes in brain activity (as measured by EEG), the neurotransmitter metabolites (as measured by MRS), and biomarkers (as measured by serum analysis) following the intervention. This comprehensive approach aids in understanding the underlying mechanisms and neurophysiological changes associated with the interventions, moving beyond the traditional focus on visual functions such as visual acuity and visual field. Additionally, the study assesses the impact of the intervention on real-world activities through gait and balance tests, as well as questionnaires evaluating mental health, QoL, and fear of falling. This holistic assessment is crucial, as the ultimate goal of vision rehabilitation is to improve functional independence and overall well-being for glaucoma patients.

While the study design is robust, there are several limitations that warrant acknowledgment. The repetitive assessments may induce learning effects across all measured outcomes, potentially limiting the ability to differentiate between true treatment effects and the effects of repeated testing. In addition, the long-term nature of the training sessions poses challenges for both participants and research staff, with fatigue and potential drop-out rates being realistic concerns in this large-scale clinical trial. Despite these limitations, it is important to recognize that if the treatment’s effectiveness is evident in the results, it could yield significant long-term benefits for glaucoma patients. Successful outcomes from this study could pave the way for the integration of tES and PL into standard vision rehabilitation protocols, potentially improving the QoL and functional independence for individuals affected by glaucoma.

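### The primary mixed model names no intervention-by-time term, so as written it cannot show an effect that grows with training or lasts afterwards, and change over visits is not a substitute

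*Protocol article*

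**What the plan says.** All places are in the protocol article.

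- **Model** (Statistical methods {20a}): "we will employ a linear mixed model with intervention type and time point as the fixed effect, and baseline MD value as the covariate". The coding is fixed too: "A dummy-coding scheme with the placebo PL + sham tES condition as the reference level will be utilized". On model building it adds: "Initially, a full model will be fitted, and if convergence issues or overfitting arise, adjustments will be made to the random intercept and slope". A likelihood-ratio test then compares the model with versions lacking the fixed effect.
- **Dose-response** (same section): "changes in MD across six time points (baseline, interim 1, interim 2, post-intervention, 1-month post-intervention, and 2-month post-intervention) will reveal the dose-response relationship". The sentence goes on to claim recovery duration as well.
- **Hypothesis** (Specific objectives, second hypothesis): "The intervention effect will increase with longer training duration". The fourth aim is to find the optimal dosage.
- **Schedule** (Intervention description {11a}; Primary outcome): every arm, placebo included, is scheduled for 30 sessions in three blocks of ten. MD is measured at all six visits, T1 to T6.
- **Limitation** (Discussion): "The repetitive assessments may induce learning effects across all measured outcomes".

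No visit is named for the primary contrast.

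**The concern.** The hypothesis concerns an arm difference that changes with the amount of training. A model with arm and time as separate fixed effects assumes that this difference does not change. What the trial wants to learn about dose and persistence is therefore ruled out by the form of the model.

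The stated substitute, change in MD across visits, does not fill the gap. Sessions completed and perimetry tests taken rise together in every arm. A rise shared equally by the placebo arm could be practice at the test and still be described as dose-response.

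A second, conditional issue is baseline. If T1 is a level of the time factor and baseline MD is also the covariate, the baseline value is used twice. The arm coefficient then averages in a visit at which the adjusted difference is zero by construction. The dB difference and interval reported would be smaller than the effect after baseline.

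**Working it through.** **1. What the stated model can estimate.** For person i in arm a at visit t, the stated fixed part is

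E(MD) = μ + α(a) + τ(t) + β × baseline MD.

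The difference between an active arm and placebo at visit t is δ(t) = α(active) − α(placebo), which has no t in it. With 10, 20 and 30 sessions at T2, T3 and T4, the dose-response trend in the arm difference is (δ(T4) − δ(T2))/2 per block. Under this model it is 0 whatever the data show. If the true differences were 1/3, 2/3 and 1 dB (assumed), it should be (1 − 1/3)/2 = 1/3 dB per block.

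The other named elements do not supply it. A random slope lets individuals depart from the common course but has mean zero in every arm. Removing arm in the likelihood-ratio test examines the average difference, and removing time examines the shared course. Neither examines growth of the effect.

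**2. What change over visits contains.** τ(t) is common to all arms. Suppose every arm gains 0.2 dB per visit from practice alone (assumed). Then τ(T4) − τ(T1) = 3 × 0.2 = 0.6 dB with no training effect at all. Only an arm-by-time contrast removes this.

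**3. If T1 is a response row (conditional).** With complete data and a random intercept only, the arm coefficient is that of an ANCOVA of each person's six-visit mean on arm and baseline B. Write P for the mean over T2 to T6:

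six-visit mean = (1/6)B + (5/6)P.

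Given B, the first term contributes nothing to the arm coefficient. The coefficient and its standard error are therefore both 5/6 of those for P.

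Three illustrative profiles, with a T4 difference of 1.0 dB (all assumed; the protocol gives no trajectory):

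| Profile, T2 to T6 | Six rows, no interaction | T2–T6, no interaction | T4 contrast with interaction |
|---|---|---|---|
| 1, 1, 1, 1, 1 | 5/6 = 0.83 | 5/5 = 1.00 | 1.00 |
| 1/3, 2/3, 1, 1, 1 | 4/6 = 0.67 | 4/5 = 0.80 | 1.00 |
| 1/3, 2/3, 1, 2/3, 1/3 | 3/6 = 0.50 | 3/5 = 0.60 | 1.00 |

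A simulation with 38 per arm, between-patient SD 4 dB and within-patient SD 1.2 dB (both assumed) gave 0.86, 0.67, 0.53 for the first column of results, 1.03, 0.80, 0.64 for the second, and 1.00 to 1.01 for the third. In the first profile the test statistics were 0.860/0.241 = 3.57 with T1 and 1.031/0.290 = 3.56 without it. Here the size of the effect is distorted and the test is not.

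**4. How far 5/6 carries.** The protocol mentions a random slope and expects 20% dropout. For a constant effect from T2, a generalised least squares check with covariance parameters held fixed gave 0.80 to 0.81 with 20% monotone dropout, and about 0.65 with an assumed random-slope SD of 0.3 dB per visit. The standard-error ratio was 0.85 to 1.00. In these settings 5/6 is not the factor and the test statistic need not be preserved.

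**5. Does the sample size settle the reading?** A regression F test with f² = 0.1, 80% power, alpha 0.05 and three predictors needs 114. Then 114/0.8 = 142.5, so 143, or 144 as a multiple of 3. This reproduces the stated 144. The three predictors could be group, time and baseline MD, or group, time and their product, so 144 does not show which model was meant.

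**The case against.** The strongest reply is that an article condenses the plan. Procedure for unblinding {17b} refers to a pre-specified statistical analysis plan for the primary and secondary analyses, which is not shown. The undefined full model could include the interaction. If it does, the T4 contrast is recoverable even with T1 kept as a response row (simulated 1.00 to 1.01). This stands as a reason to ask what was meant. It does not clear the text, which lists two fixed effects, names only random terms as open to adjustment, and sits beside a hypothesis that this model cannot test.

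A reader might infer that the plan certainly uses baseline twice. The documents do not support that. The model sentence lists no levels for time, and the six-visit list belongs to a separate sentence on what changes in MD will show. A baseline covariate fits a T2 to T6 response equally well.

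A reader might also infer that the reported effect will be a third to a half too small. That takes T4 as the truth, while the protocol names no primary visit, and it relies on invented trajectories. An average over visits is a legitimate estimand and a more precise one. The gap in the column without T1 is averaging, not error.

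Finally, effectiveness is to be judged by comparing arms, and test learning is openly disclosed. Both are true, but the disclosure does not repair the sentence that takes dose-response from change over time.

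**Conclusion.** The concern holds in this form. As written, the primary model gives one time-constant difference per active arm. It cannot test the second hypothesis or estimate arm-specific dose-response and durability. That follows from the form of the model and needs no assumed figure. Reading dose-response from change in MD across visits confounds training with repeated testing.

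The baseline issue is conditional. If T1 is a response row and no interaction is fitted, the arm coefficient is 5/6 of the post-baseline average, 17% smaller, under a random intercept with complete data, and the test statistic is nearly unchanged. With dropout or random slopes the factor differs. If T1 is not a response row, this part falls away and the missing interaction remains. Nothing here shows an inflated type I error for the averaged arm comparison.

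**What to change.** In Statistical methods {20a}:

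1. Use MD at T2 to T6 as the response, with fixed effects for arm, categorical time, arm-by-time and baseline MD. Alternatively, keep T1 as a response with a common baseline mean across arms and drop the covariate.
2. Name the primary contrast in advance, for example the arm difference at T4, the end of training. If an average over post-baseline visits is preferred, say so.
3. Define dose-response as the trend in the arm difference over T2, T3 and T4, and durability as the arm difference at T5 and at T6.
4. Replace the sentence that reads dose-response from change over time with those definitions.
5. State which fixed effects the full model contains.

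The cost is wording, plus precision if a single visit is chosen. In the simulation the T4 contrast had a standard error of about 0.38 against 0.29 for the T2 to T6 average, a ratio of 0.38/0.29 = 1.31.

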### Sample size {14}

The sample size calculation for linear multiple regression with three groups and six time points was performed using G*Power (version 3.1). According to the HRP results from phase 1 study [37] in the GREAT project (Cohen’s *f*^2^ = 0.1), a sample of 144 glaucoma patients will be needed to provide 80% power to detect a significant difference in visual field among three groups at the 2-tailed 0.05 alpha level, assuming a 20% dropout rate.

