### Methods in analysis to handle protocol non-adherence and any statistical methods to handle missing data {20c}

Missing data will be conducted by an intent to treat analysis (all randomized participants will be included with the last value carried forward), followed by a secondary “per-protocol” analysis (include only participants who followed all aspects of the protocol correctly).

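### FCS multiple imputation is credited with guarding against non-random dropout, but as described it assumes missing at random and cannot test for that

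*Protocol article*

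**What the plan says.** Section {20a} of the protocol article (statistical methods for primary and secondary outcomes) sets the model for 24-2 mean deviation (MD): "we will employ a linear mixed model with intervention type and time point as the fixed effect, and baseline MD value as the covariate". For missing data it adds a sensitivity analysis by multiple imputation, in which "we will employ the fully conditional specification (FCS) method". The stated purpose is broad: "we aim to assess the robustness of our primary analysis results to potential attrition bias and missing data". The paragraph closes by saying that multiple imputation handles the problem in a principled way, "ensuring that our conclusions are not unduly influenced by the potential non-random nature of missing data".

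The article describes no delta adjustment, reference-based imputation, pattern-mixture model or selection model.

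Three other places bear on the point:

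- Section {20c} gives a different rule for the intention-to-treat analysis, in which "all randomized participants will be included with the last value carried forward", followed by a per-protocol analysis.
- Section {14} sizes the trial at 144, "assuming a 20% dropout rate".
- The Discussion lists "fatigue and potential drop-out rates being realistic concerns in this large-scale clinical trial".

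**The concern.** Standard FCS fills in a missing MD from its distribution given the observed data. That is valid when dropout depends only on what has been observed (missing at random). It gives no information about patients whose unseen values differ systematically from those of comparable patients who stayed. The closing sentence of {20a} therefore credits the method with a protection it does not supply.

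Such dropout is plausible here. Treatment is thirty sessions of about an hour at two to three a week, with six assessments, and patients may leave through fatigue or because they feel no benefit in a way that earlier MD readings do not capture.

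What is at stake is interpretation. If the mixed model and the FCS analysis agree, the trial report could present this as evidence that non-random dropout did no harm, when that possibility was never examined.

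**Working it through.** **1. The plan's own figure.** The sample size is not disputed. Taking f² = 0.1, two-sided alpha 0.05 and 80% power in a multiple-regression F test, and assuming three tested predictors (the number is not stated), N = 114. Then 114/(1 − 0.2) = 142.5, rounded up to 143, or 144 for three equal arms of 48. Nothing below changes this.

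**2. Assumptions side by side.**

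| Analysis | Where | Assumption about unseen MD |
|---|---|---|
| Mixed model on observed data | {20a} | Missing at random |
| FCS multiple imputation, as described | {20a} | Missing at random |
| Last value carried forward | {20c} | Unseen value equals the last observed one |
| Per-protocol | {20c} | Restricts the sample; no explicit model for unseen values |

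None of these varies the assumption about unseen values in a controlled way.

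**3. Does FCS reveal non-random dropout?** An illustrative simulation used two arms of 48, six visits and 400 replicates per mechanism. Its inputs are assumptions, not taken from the documents: baseline SD 5 dB, visit noise SD 1 dB, response SD 1 dB, true difference 1.0 dB, and dropout by T6 of about 13% (placebo) and 18% (active). In the active arm, dropout became more likely as the change in MD worsened. The change that drove it was the previous, observed one (at random) or the current, unseen one (not at random). The mixed model was represented by maximum likelihood with unstructured covariance; FCS used 10 imputations. Mean estimates of the T6 difference, in dB:

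| Dropout | Full data | Mixed model | FCS | Last value forward |
|---|---|---|---|---|
| At random | 0.98 | 0.99 | 0.99 | 0.80 |
| Not at random | 1.01 | 1.20 | 1.19 | 1.05 |

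Under non-random dropout FCS kept essentially all of the mixed model's bias: 1.19 − 1.01 = 0.18 dB, against 1.20 − 1.01 = 0.19 dB. Under both mechanisms the two estimates correlated 0.994 across replicates and differed on average by 0.03 dB in absolute terms, against a sampling SD of about 0.38 dB. The size of the bias depends on the inputs. The near-identity follows from the two methods using the same observed-data distributions.

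FCS differed from last value carried forward under both mechanisms (0.99 − 0.80 = 0.19 dB and 1.19 − 1.05 = 0.14 dB). A gap between those two methods is therefore not a sign of non-random dropout either. That carrying forward lands near the full-data value in the second row is a feature of this set-up and does not support the method.

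**4. Size of an undetected departure.** Let m be the fraction missing in an arm and δ the difference between the true unseen values and those imputed under missing at random.

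- Shift in the arm's mean = m × δ. With m = 0.20: δ = 1 dB gives 0.2 dB; δ = 2 dB gives 0.4 dB.
- Shift in a two-arm contrast = m₁δ₁ − m₂δ₂. With equal m and equal δ this is 0.

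For scale, 48 × 0.8 = 38.4, so about 38 per arm. A contrast of change from baseline has SE = √(4 × SD²/38), where SD is the within-person SD of one MD reading. The documents give no such SD, so a range is shown:

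| Assumed SD (dB) | SE (dB) | 0.4 dB as a multiple of SE |
|---|---|---|
| 0.8 | 0.26 | 1.5 |
| 1.2 | 0.39 | 1.0 |
| 2.0 | 0.65 | 0.6 |

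Placing the full 20% at one visit is also an assumption, since {14} gives a single rate without timing.

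**The case against.** **The primary analysis may not be the mixed model on observed data.** Under {20c} it may use last value carried forward, which is not a missing-at-random method. This stands as a limit. A reader might infer that the FCS analysis merely repeats the primary one. The documents do not support that without condition, because {20a} and {20c} conflict on which rule governs. It does not rescue the sentence, since FCS fails to address non-random missingness under either rule.

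**FCS may use more variables than the mixed model.** The article values FCS for handling several variables with different distributions, and VFI, PSD and high-resolution perimetry are measured from T1 to T6. Using them could make missing at random more credible and move FCS away from the mixed model. That stands against any claim that the two must coincide. It would still not test departures from the assumption.

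**Non-random may mean only not completely at random.** The article uses no formal taxonomy. On this softer reading, FCS does cover dropout that depends on observed values, but so does a mixed model on observed data, and the sensitivity analysis then adds little.

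**Details belong in the statistical analysis plan.** Delta grids are often left there, and section {17b} refers to a pre-specified plan that is not shown. A reader might infer that no analysis of non-random dropout exists; the article's silence does not establish that. The point rests on what the article states: it names FCS and attributes the protection to multiple imputation itself. A further analysis in another document would not make that sentence correct.

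**Conclusion.** The concern holds in this form: the protection claimed in {20a} is not a property of standard FCS, and the sensitivity analysis as described cannot show robustness to non-random dropout. If the primary analysis is the mixed model on observed data, close agreement with FCS is expected in either case, less so if FCS draws on auxiliary variables. If it rests on last value carried forward, the assumptions differ but the gap remains.

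The size is illustrative. With 20% missing in one arm, a 2 dB departure moves that arm's mean by 0.4 dB, about 0.6 to 1.5 standard errors for an assumed SD of 2.0 down to 0.8 dB. It moves the contrast by nothing if missingness and departure are equal in both arms. A reader might infer that the treatment estimate will be biased by this amount. The documents do not support that: they give no SD for MD, no dropout timing and no evidence that dropout will differ by arm.

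The consequence is for how robustness is interpreted. Sample size, type I error and the primary model are unaffected. It should be corrected before unblinding.

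**What to change.** 1. Reword the closing sentence on multiple imputation in {20a} to say that FCS assumes missing at random given the variables in the imputation model, and that only the analyses in step 2 examine departures from it.
2. Pre-specify two departures on the same FCS engine:
   - Delta-adjusted imputation, with imputed MD shifted in steps until the conclusion changes. The sponsor should justify the grid and let deltas differ by arm, because equal shifts with equal missingness cancel.
   - Placebo-reference imputation, in which dropouts from the two real-PL arms follow the trajectory of the placebo PL + sham tES arm.
3. Reconcile {20a} with {20c}: state which missing-data rule governs the primary analysis and what role, if any, last value carried forward keeps.
4. List the variables in the imputation model, including any auxiliary ones.

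The cost is a few more analysis runs and some text; no extra patients or visits are needed. The downside is that the results may look less robust than under the present plan.
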